| Study Center(s)                       | Single Center                                                                                                                                                                                                                                  |
| Primary Objective                     | The primary end-point of the study is to determine the sensitivity of SGM-101 in identifying lung nodules when excited by a near-infrared light source.                                                                                        |
| Secondary Objective                   | The secondary objective is to measure the concordance of fluorescence and tumor type.                                                                                                                                                          |
| Number of Subjects                    | We intend to enroll 20 lung cancer subjects in this study.                                                                                                                                                                                     |
| Diagnosis and Main Inclusion Criteria | The study is focusing on subjects presenting with suspected malignancies of the lung and pleura who are considered to be good surgical candidates.                                                                                             |
| Study Product, Dose, Route, Regimen   | SGM-101 is a fluorescent conjugate comprised of a tumor-specific, anti-carcinoembryonic antigen (CEA) monoclonal antibody and a near infrared (NIR) emitting fluorochrome. We will give 5 to 10 mg intravenously 3 to 5 days prior to surgery. |
| Duration of administration            | The proposed dose of SGM-101 to be investigated in this study is 10 mg to be administered intravenously over 30-60 minutes.                                                                                                                    |
| Reference                             | Non-placebo controlled                                                                                                                                                                                                                         |

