## **2 Study Objectives**

### **Primary Objective**

The primary study objectives are to assess the sensitivity and specificity of SGM-101 in detecting non-small cell lung carcinomas during surgery.

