| Disease present
("The Truth")   | True
( $H_0$ )  | TP
( $1 - \beta$ )                              | FN
(type 2 error = $\beta = 1 - \text{sens}$ ) | $\text{sensitivity} = \frac{TP}{TP + FN}$                                 |
|                                    | False
( $H_A$ ) | FP
(type 1 error = $\alpha = 1 - \text{spec}$ ) | TN
( $1 - \alpha$ )                            | $\text{specificity} = \frac{TN}{TN + FP}$                                 |
| Data Analysis                      |                    | $PPV = \frac{TP}{TP + FP}$                         | $NPV = \frac{TN}{TN + FN}$                        | $\text{Accuracy} = \text{efficiency} = \frac{TP + TN}{TP + TN + FP + FN}$ |

True positive = fluorescent nodule, pathology is cancer

False positive = fluorescent nodule, pathology is no cancer

True negative = not fluorescent nodule, pathology is no cancer

False negative = not fluorescent nodule, pathology is cancer

Cohort 1: Our first 10 subjects will be a feasibility trial. We will discover whether lung non-small cell lung cancers fluoresce based on the intraoperative images. The surgeon will look at the images during surgery to determine if the tumor is glowing or not. Based on prior experience, we will be cautious for false positives. In our first 10

subjects, if we have 5 or more subjects with a false positive, then we will review the data prior to proceeding. If we have a high false positive rate, then we will likely not proceed because the clinical value of the fluorescent probe is minimal. (Of note, if the first five consecutive patients have false positives, we will stop the study and analyze the data carefully before we will consider proceeding).

Cohort 2: If the first 10 subjects show no significant false positives, then we will perform another 10 subjects. The primary goal will be to determine (a) how many non-small cell lung cancers are detected by intraoperative imaging? Additional data will be collected to determine (b) how deep the imaging system can see into the lung organ, (c) can metastatic cancer cells in lymph nodes and satellite nodules be detected? (d) if the surgeon mistakenly cuts through the tumor, will the intraoperative imaging detect a positive margin? In this cohort, we will not make any clinical decisions to jeopardize the patient or remove significantly more than the intended operation. We will collect more data in this cohort for analysis.

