### 3.2 Study Endpoints

#### Efficacy

Efficacy will be assessed through determination of the sensitivity and specificity of SGM-101 uptake and expression in identifying non-small cell lung cancer. Additional exploratory efficacy outcomes will include:

- Number of lung nodules lesions identified under usual visual/tactile conditions compared with such lesions identified using SGM-101 and fluorescence imaging
- Number of lymph nodes with metastatic cancer that are identified using visual/tactile conditions compared with such lesions identified using SGM-101 and fluorescence imaging
- Proportion of subjects in whom more lesions are identified using SGM-101 with fluorescence imaging and subsequently confirmed by pathology/immunohistochemistry analysis as cancer compared with using usual visual/tactile conditions to identify such lesions
- Number of cases that surgeon cuts through tumor and the positive margin is detected by the imaging of SGM-101.

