## 4 Subject Selection and Withdrawal

### 4.1 Inclusion Criteria

1. Adult subjects over 18 years of age
2. Subjects presenting with a lung, pleural nodule or mass presumed to be resectable on pre-operative assessment
3. Good operative candidate
4. Subject is capable of giving informed consent and participating in the process of consent.

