The sensitivity will be based on the single lung nodule that is being removed in a patient. Typically for lung cancer surgery, we are there to remove one nodule. That will be the basis of the calculations. Thus, the denominator will be 10 patients for the first Cohort, and another 10 patients for the second Cohort. (A total of 20 data points for the whole study). The calculations will be based on two pieces of data: tumor fluorescence and pathology. We will not be doing a detailed IHC study at this time.

If successful, we will consider 10 more subjects. Then, with 20 subjects, we will have 90% power to identify any unforeseen adverse event that occurs with a prevalence of at least 5%. We will use a Bayesian continuous safety monitoring design that registers a signal if the posterior probability that the chance of an adverse reaction is greater than 0.1 exceeds 80%. If we encounter a safety signal, we will suspend enrollment until the issue has been addressed.

The fraction of tumors on pathology that are identified by the imaging procedure will provide an estimate of the sensitivity of the procedure. Of the 20 enrolled subjects, we expect approximately 60%, or 12, to have fluorescent tumors. With 12 tumors, an exact 95% confidence interval for sensitivity would range from (0%, 12%) if no tumors are detected up to (88%, 100%) if all 12 are detected. We will compute estimates of the sensitivity (fraction of path-positive margins that are called correctly) and specificity (fraction of path-negative margins that are called correctly), and calculate 95% confidence intervals around them. A second aim will be to estimate the sensitivity of the procedure for identifying all lesions, including lesions that were not pre-identified. Because some subjects will contribute more than one lesion, we will estimate these parameters using random effects logistic regression models (in SAS Proc Glimmix) that allow for between-subject variability. These specimens will provide independent estimates of the positive and negative predictive values of discovering satellite nodules.

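### The primary sensitivity and specificity have conflicting definitions (NSCLC, any cancer, lung nodules, resection margins); the margin sentence in 7.1 is wrong as written, and the any-cancer table matches the NSCLC objective only if no other malignancy is resected

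*Protocol*

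**What the plan says.** The protocol describes the target of its primary accuracy measures in several places.

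- **Section 2, Primary Objective:** "The primary study objectives are to assess the sensitivity and specificity of SGM-101 in detecting non-small cell lung carcinomas during surgery".
- **Section 3.2, Efficacy:** "Efficacy will be assessed through determination of the sensitivity and specificity of SGM-101 uptake and expression in identifying non-small cell lung cancer". In 3.1, the main goal of cohort 2 is likewise the number of NSCLCs that imaging detects.
- **Study Summary, Primary Objective:** "determine the sensitivity of SGM-101 in identifying lung nodules when excited by a near-infrared light source". This gives no histology and names sensitivity only. The synopsis row on statistical methodology names both measures, with microscopic pathology as the reference.
- **2x2 table, printed in 3.1 and again in 7.1:** "True positive = fluorescent nodule, pathology is cancer". The other three cells follow the same pattern. The unit is the nodule and the reference is cancer or no cancer, without type.
- **Section 7.1, the sentence on what will be computed with 95% confidence intervals:** "estimates of the sensitivity (fraction of path-positive margins that are called correctly) and specificity (fraction of path-negative margins that are called correctly".
- **Section 7.1, elsewhere:** sensitivity rests on the one nodule removed per patient, which is named as the basis of the calculations and gives 20 data points. Sensitivity is also described as the share of pathology-confirmed tumors that imaging finds. Section 7.2 repeats that each patient contributes one nodule or cancer.

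Eligibility in 4.1 is wider than NSCLC: "Subjects presenting with a lung, pleural nodule or mass presumed to be resectable on pre-operative assessment". Apart from the 7.1 sentence, the plan treats margins as additional cohort 2 data (3.1) and as an exploratory count of cases in which the surgeon cuts through tumor (3.2).

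**The concern.** A sensitivity needs one unit, one reference condition and one denominator. Here the unit is a nodule in some places and a margin in another. The reference condition is NSCLC in the objective and endpoint, but any cancer in the table that the analysis is said to follow. Nothing in the protocol says which wording governs.

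Two consequences follow. First, an analyst who takes the margin sentence at its word would report a quantity that is not the primary objective. Second, an analyst who takes the table at its word would count a fluorescent non-NSCLC malignancy as a true positive, and a non-fluorescent one as a false negative, in a figure labelled as NSCLC detection. In a study of 20 subjects a few such nodules move the result, and the choice between definitions could be made after the results are known.

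**Working it through.** **1. Unit: margin or nodule.** Set side by side:

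| Place | Unit | Role |
|---|---|---|
| 3.1 and 7.1, 2x2 table | nodule | the announced analysis |
| 7.1, basis of calculations | one removed nodule per patient, 20 data points | denominator |
| 7.1, share of tumors found | tumor on pathology | estimate of sensitivity |
| 7.2 | one nodule or cancer per patient | denominator |
| 7.1, margin sentence | resection margin | what will be computed with 95% intervals |
| 3.1 (cohort 2) and 3.2 | margin | additional data, exploratory count |

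The sentence after the margin sentence introduces a second aim, covering all lesions. The margin sentence therefore stands where the primary estimate belongs. It is also the only place in the prose of 7.1 that says how specificity is calculated; the other definition is the table. It fits none of the nodule-level statements. A margin-based result cannot be worked out from the document, which gives neither a number of margins nor a positive-margin rate.

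**2. The plan's own figure.** For 12 tumors, 7.1 gives exact 95% intervals of 0% to 12% (none detected) and 88% to 100% (all detected). The exact upper limit at 0/n is 1 − 0.025^(1/n). With n = 12 this is 1 − 0.025^(1/12) = 26.5%, and the lower limit at 12/12 is 73.5%. The stated interval does not reproduce. That is a separate error, and the present point does not depend on it.

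**3. Reference condition: any cancer or NSCLC.** Inputs:

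- 20 subjects, one nodule each (7.1, 7.2).
- 90% of suspected lung cancers prove to be cancer (3.1): 20 × 0.90 = 18 cancers and 2 non-cancers. The 3.1 figure is for lung cancer; here it is taken as the share that is cancer of any type.
- 12 fluorescent tumors, 60% of 20 (7.1).
- k = number of the 18 cancers that are not NSCLC. The protocol gives no share, so k = 0 to 4 is an assumption.

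Any-cancer sensitivity = 12/18 = 66.7% (exact 95% interval 41.0% to 86.7%). On the denominator of 20 stated in 7.2, the same 12 would give 12/20 = 60.0% (36.1% to 80.9%).

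NSCLC sensitivity is (12 − k)/(18 − k) if all k other cancers fluoresce, and 12/(18 − k) if none do:

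| k | all k fluoresce | none fluoresce |
|---|---|---|
| 0 | 12/18 = 66.7% | 12/18 = 66.7% |
| 1 | 11/17 = 64.7% | 12/17 = 70.6% |
| 2 | 10/16 = 62.5% | 12/16 = 75.0% |
| 3 | 9/15 = 60.0% | 12/15 = 80.0% |
| 4 | 8/14 = 57.1% | 12/14 = 85.7% |

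At k = 4 the exact 95% intervals are 28.9% to 82.3% for 8/14 and 57.2% to 98.2% for 12/14. The any-cancer figure can therefore overstate or understate NSCLC sensitivity, and the two agree for certain only at k = 0.

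**4. Specificity.** With cancer as the reference, the denominator is the 2 expected non-cancers. If disease-positive became NSCLC and other malignancies were moved into the not-diseased group, it would be 2 + k, up to 6. The plan must therefore say where those nodules go. Tabulating them separately leaves specificity on the benign nodules.

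**The case against.** The strongest defence is that the intent is clear. Section 7.1 states that the single removed nodule is the basis of the calculations, the table scores nodules, 7.2 agrees, and margins enter through one parenthetical definition. This stands in part: the margin wording is best read as one faulty sentence, not as the design. A reader might go further and infer that the primary sensitivity will have almost no denominator, because positive margins are rare. The documents do not support that. They give no margin rate and no number of margins per subject, and their repeated nodule statements point away from such an analysis.

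On the reference condition, 3.1 describes candidates as having nodules suspicious for NSCLC, and the synopsis speaks of 20 lung cancer subjects, so other malignancies may be few. That is fair, but neither statement is an eligibility criterion, and 4.1 is open to any resectable lung or pleural nodule or mass. A reader might also infer that the result will be biased upward, because the earlier colorectal and pancreas study reported 97% sensitivity at 10 mg and a lung metastasis would fluoresce as readily. This does not follow. Section 1.4 says that study's conclusions on concordance rest on in-vivo and ex-vivo readings combined, whereas here the surgeon judges fluorescence during surgery. The population differs, and nothing in the protocol gives a number of metastases. The direction is open, as the table shows.

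It can also be said that any lung cancer is a defensible target, since the hypotheses in 7.2 are worded that way, and that the study is a descriptive pilot from which an NSCLC figure could be derived later by tumor type. Both are true. They reduce the harm but do not settle which figure is primary.

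**Conclusion.** The point holds as an inconsistency in the definition of the primary measures. The margin sentence in 7.1 is wrong as written: it contradicts the 2x2 table and the 20 nodule-level data points, and it gives primary status to something that is otherwise exploratory. The any-cancer table equals the NSCLC objective in Sections 2 and 3.2 only if no other malignancy is resected, which 4.1 does not ensure.

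On the protocol's own expectations (18 cancers, 12 fluorescent) and an assumed 0 to 4 cancers that are not NSCLC, the primary sensitivity would be between 57% and 86% instead of 67%. That is up to about 10 points lower or 19 points higher. These shifts lie within the 41% to 87% interval around 12/18, so this is a matter of what the headline figure means more than of precision. The range depends on the assumed number of other cancers; the contradiction does not.

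**What to change.** - **7.1:** replace margins with nodules in the sentence on what will be computed. Suggested wording: *Primary sensitivity is the proportion of pre-identified, resected nodules with final pathology of NSCLC that are fluorescent on intraoperative imaging. Primary specificity is the proportion of such nodules with no cancer on final pathology that are not fluorescent. Each is given with an exact 95% confidence interval.*
- **2x2 table and its legend, in 3.1 and 7.1:** define disease-positive for the primary analysis as final pathology of NSCLC, to match Sections 2 and 3.2.
- **Other malignancies:** report them outside the primary table by tumor type, under the existing secondary objective, and give any-cancer sensitivity as a supporting estimate.
- **False positives:** state that fluorescent benign nodules remain the false positives, and that the cohort 1 false-positive review rules keep their present not-cancer definition. This change is not meant to alter them.
- **Margins:** keep margin detection as the exploratory count already in 3.2.
- **Synopsis:** align the primary objective with Section 2 on both measures and the target condition.

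The cost is wording in the synopsis, 3.1 and 7.1. Fluorescence and pathology are already collected, and tumor type is needed for the secondary objective. The one statistical downside is a slightly smaller primary sensitivity denominator if other cancers are enrolled: 14 instead of 18 at the far end of the assumed range.

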## 7.2 Statistical Methods

All data will be summarized, with means and standard deviations for continuous variables and proportions for categorical variables. Graphical techniques will be used for data exploration. Analyses will be primarily descriptive. The remainder of the statistical approaches is described above.

Null hypothesis = Lung cancers will not fluoresce with a CEA-targeted dye.

Alternative hypothesis = Lung cancers will fluoresce with a CEA-targeted dye.

Alpha = 0.25

Beta = 0.5

There are 20 patients, thus the denominator will be 20.

Each patient will contribute one nodule or cancer to the study.

Patients with more than one nodule typically do not get surgery because that represents metastatic disease and is considered non-surgical.

## 8 Safety and Adverse Events

### 8.1 Definitions

#### Unanticipated Problems Involving Risk to Subjects or Others

Any incident, experience, or outcome that meets all of the following criteria:

1. Unexpected in nature, severity, or frequency (i.e. not described in study-related documents such as the IRB-approved protocol or consent form, the investigators brochure, etc.)
2. Related or possibly related to participation in the research (i.e. possibly related means there is a reasonable possibility that the incident experience, or outcome may have been caused by the procedures involved in the research)

3. Suggests that the research places subjects or others at greater risk of harm (including physical, psychological, economic, or social harm).

All events that occur and meet the Common Terminology Criteria for Adverse Events (CTCAE version 4) published by the U.S. Department of Health and Human Services will be reported.

#### Adverse Event

An **adverse event** (AE) is any symptom, sign, illness or experience that develops or worsens in severity during the course of the study. Intercurrent illnesses or injuries should be regarded as adverse events. Abnormal results of diagnostic procedures are considered to be adverse events if the abnormality:

1. results in study withdrawal
2. is associated with a serious adverse event
3. is associated with clinical signs or symptoms
4. leads to additional treatment or to further diagnostic tests
5. is considered by the investigator to be of clinical significance

#### Serious Adverse Event

Adverse events are classified as serious or non-serious. A **serious adverse event** is any AE that is:

1. fatal
2. life-threatening
3. requires or prolongs hospital stay
4. results in persistent or significant disability or incapacity
5. a congenital anomaly or birth defect
6. an important medical event

Important medical events are those that may not be immediately life threatening, but are clearly of major clinical significance. They may jeopardize the subject, and may require intervention to prevent one of the other serious outcomes noted above. For example, drug overdose or abuse, a seizure that did not result in in-subject hospitalization or intensive treatment of bronchospasm in an emergency department would typically be considered serious. All adverse events that do not meet any of the criteria for serious should be regarded as non-serious adverse events.

#### Adverse Event Reporting Period

The study period during which adverse events must be reported is from the time the subject checks-in for SGM 101 study dye infusion visit until completion of subject's post-operative visit (approximately 2-4 weeks after visit 3 date of surgery). The following common surgical adverse events with a start date occurring after the subject's surgical procedure has begun will not be captured unless the adverse event remains a grade 4 at discharge: pain, Nausea, Vomiting, Fatigue, Inflammation, Swelling, Tenderness at the site of incision, Pneumothorax, Atelectasis, Hemothorax,

Hydropneumothorax, Drain placement for fluid retention and air leak, Excision site pain, Atrial Fibrillation, Renal Insufficiency, Constipation, Anemia, Sinus Bradycardia, Crepitus, Stress, Urinary Retention, Drowsy, Light headedness, Headache, Pneumonia, Hypotension, Hypertension, Frustration, Irritability, Restlessness, and Insomnia.

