#### Safety

The safety of the study will be determined via incidence rates of all AEs and treatment-emergent AEs (TEAEs) from the time of SGM-101 administration through follow-up.

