### 5.2 Treatment Regimen

The proposed dose of SGM-101 to be explored in this study is 5-10 mg to be administered intravenously over 30 minutes followed by a 50 mL flush of isotonic saline to account for the dead volume of the tubing. SGM-101 will be administered 3 to 5 days (+/-1 day) prior to surgery..

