### 8.2 Recording of Adverse Events

At each contact with the subject while on the study, the investigator must seek information on adverse events by specific questioning and, as appropriate, by examination. Information on all adverse events should be recorded immediately in the source document, and also in the appropriate adverse event module of the case report form (CRF). All clearly related signs, symptoms, and abnormal diagnostic procedures results should be recorded in the source document, though should be grouped under one diagnosis.

The clinical course of each adverse event should be followed until resolution, stabilization, or until it has been determined that the study treatment or participation is not the cause. Serious adverse events that are still ongoing at the end of the study period must be followed up to determine the final outcome. Any serious adverse event that occurs after the study period and is considered to be related to the study treatment or study participation should be recorded and reported immediately.

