#### **8.4 Reporting SAE's to the DSMC**

All on-site SAEs for Penn subjects regardless of attribution or expectedness must be submitted to the DSMC within 10 days. Reports will be sent to the DSMC for **90 days** following the last date the subject received study treatment/therapy or was exposed to an investigational device.

All unexpected deaths or deaths related to the study agents/device must be reported within 24 hours. All other deaths should be reported within 30 days.

All adverse events which meet the following criteria will also be managed as described below:

All Grade 3 or higher events will be reported to the DSMC within 10 days of knowledge of the event. All unexpected deaths will be reported within 24 hours of knowledge of the event.

All other deaths will be reported within 30 days of knowledge of the event.

In addition, any adverse events will be recorded promptly in CTMS (clinical research management database).

In addition, any adverse events will be recorded in CTMS (clinical research management database).

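### Scheduled adverse event collection ends about 16 to 34 days after dosing, but section 8.4 requires all on-site SAEs for 90 days, and new SAEs judged unrelated are not sought in between

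*Protocol*

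**What the plan says.** Section 8.1 (Adverse Event Reporting Period) sets the period in which adverse events must be reported as "from the time the subject checks-in for SGM 101 study dye infusion visit until completion of subject's post-operative visit", and dates that end point as the "post-operative visit (approximately 2-4 weeks after visit 3 date of surgery"). The Schedule of Procedures lists AE assessments at Visits 2, 3 and 4 only. Visit 4, the post-operative follow-up, is the last visit.

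Section 8.4 sets a different rule: "All on-site SAEs for Penn subjects regardless of attribution or expectedness must be submitted to the DSMC within 10 days". It continues: "Reports will be sent to the DSMC for 90 days following the last date the subject received study treatment/therapy", and adds exposure to an investigational device as a second way of starting that clock.

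Three provisions reach past Visit 4:
- Section 8.1 (Post-study Adverse Event): unresolved events are followed, and subjects are told at the last visit to report later events that they or their physician think may be related to the study.
- Section 8.2: "Any serious adverse event that occurs after the study period and is considered to be related to the study treatment" or to study participation is to be recorded and reported at once. SAEs still ongoing at the end of the study period are followed to their outcome.
- Section 8.3: adverse events that are both unexpected and related go to the IRB, whether they occur during or after the study.

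Section 8.2 requires specific questioning about adverse events only at contacts made while the subject is on study.

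**The concern.** The two windows differ in length and in scope. The 8.1 period closes a few weeks after surgery. The 8.4 period runs to 90 days and disregards attribution. Between them, every route by which a new event could reach the site depends on someone believing that it is related. A new hospitalization on day 50 that nobody links to the agent falls under 8.4, but no visit, call or instruction would bring it in.

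This matters because the trial has 20 subjects and the clinical studies of the agent described in section 1.4 were in gastrointestinal and pancreatic disease, not lung surgery. One unreported subject with an SAE is 1/20, or 5 percentage points, of the 90-day SAE proportion that the DSMC would see. A committee that receives no late reports cannot tell whether there were no events or nobody asked. Filtering late events by perceived relatedness also defeats the purpose of a rule that ignores attribution.

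Section 8.1 leaves a second, smaller gap. Its end point is a visit dated from surgery. Section 4.4 withdraws a subject who decides against surgery. If the dose has already been given, no post-operative visit exists to close the period.

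**Working it through.** The 90 days is a stated rule rather than a derived figure, so there is nothing to reproduce. The check is calendar arithmetic.

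**Inputs**
- Dosing to surgery (section 5.2): "SGM-101 will be administered 3 to 5 days (+/-1 day) prior to surgery", so 3 to 5 days nominally and 3 - 1 = 2 to 5 + 1 = 6 days with the tolerance.
- Alternative wording in sections 3.1 and 6.2: up to 5 days before surgery, read here as 0 to 5 days.
- Surgery to Visit 4 (section 8.1): 2 to 4 weeks, or 14 to 28 days.
- DSMC window (section 8.4): 90 days from last treatment, or from device exposure. If the imaging camera counts as an investigational device, that clock starts on the day of surgery.

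**Formulas**
- Days covered = (days from start of clock to surgery) + (14 to 28).
- Days not covered = 90 - days covered. Share = days not covered / 90.

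Main case, section 5.2 with its tolerance:
- Earliest end: 2 + 14 = 16 days. Not covered: 90 - 16 = 74 days; 74/90 = 82%.
- Latest end: 6 + 28 = 34 days. Not covered: 90 - 34 = 56 days; 56/90 = 62%.

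| Start of clock and interval | Scheduled collection ends (day) | Days of 90 not covered | Share |
|---|---|---|---|
| Dosing, 3 to 5 days before surgery | 17 to 33 | 57 to 73 | 63% to 81% |
| Dosing, 2 to 6 days (with tolerance) | 16 to 34 | 56 to 74 | 62% to 82% |
| Dosing, 0 to 5 days (up to 5 days) | 14 to 33 | 57 to 76 | 63% to 84% |
| Device exposure, day of surgery | 14 to 28 | 62 to 76 | 69% to 84% |

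Under every reading, more than half of the window lies after the last scheduled assessment.

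**What is captured between Visit 4 and day 90**

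| Type of event | Provision |
|---|---|
| AE unresolved or SAE ongoing at last visit | Followed (8.1, 8.2) |
| New event believed related | Subject report (8.1), related SAE rule (8.2), IRB rule if also unexpected (8.3) |
| New SAE not believed related | Required by 8.4; no provision to find it |

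The gap is the last row.

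**The case against.** The strongest reply is that section 8.4 is a duty to submit reports, not to search for events. Its deadlines for Grade 3 or higher events and for deaths run from when the event becomes known. A collection period for adverse events and a longer submission period for SAEs can coexist, and a single-centre site whose surgeons recruit their own patients can send on whatever it learns. This stands in part. A reader might infer that a site following 8.1 and the schedule cannot comply with 8.4, but the text does not go that far. What remains is incomplete ascertainment of a class of events that 8.4 names without restriction.

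A reader might also infer that most of the 90-day window goes unobserved. The documents do not support that. Passive capture of related events, and follow-up of events already open, continue after Visit 4 under 8.1, 8.2 and 8.3.

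A third tempting inference is that the safety endpoint in section 3.2 is contradicted. That endpoint runs "from the time of SGM-101 administration through follow-up", and the schedule labels Visit 4 as the post-operative follow-up, so 3.2 can be read consistently with 8.1. The conflict concerns reporting to the DSMC.

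On urgency, section 1.2 gives preliminary half-lives of 16.9 to 36.3 hours. The earliest Visit 4, at day 16 (16 × 24 = 384 hours), is 384/36.3 = 10.6 half-lives after the dose even at the longest value. That makes late drug-related events less likely without excluding them. It does not answer a rule that applies regardless of attribution.

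For the dosed subject without surgery, section 4.4 does monitor anyone discontinued because of an adverse event until resolution or stability. It says nothing for one who simply declines the operation.

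**Conclusion.** The conflict is real but limited. Sections 8.1 and 8.4 set different safety windows. With section 5.2 dosing and its tolerance, 56 to 74 of the 90 days after dosing (62% to 82%) have no scheduled ascertainment. If the camera is an investigational device for the purposes of 8.4, the figure is 62 to 76 days (69% to 84%). The events affected are new SAEs not believed related, which would be under-counted against what 8.4 requires. By how much cannot be said, because the protocol gives no late SAE rate. Section 8.1 also has no end date for a dosed subject who does not have surgery, which could concern at most a few of the 20.

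The size rests on three assumptions: Visit 4 falls within its approximate 14 to 28 days, no unscheduled contact is counted, and either reading of the 8.4 clock is possible. No sample size, alpha, power or sensitivity estimate changes. The point should be corrected because two stated rules disagree and the repair is cheap.

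**What to change.** Reconcile the reporting period in 8.1, the after-study rule in 8.2 and the DSMC rule in 8.4 to one SAE window. State its start explicitly: the infusion, or device exposure if the camera counts as an investigational device. This choice matters, because a 90-day window counted from the infusion would close earlier than 8.4 requires under the device reading. Define the end so that it also applies to a dosed subject who has no surgery.

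Then take one of two routes:
- If the 90-day requirement stands, add to the Schedule of Procedures one hospital-record check or telephone contact for SAEs at the end of that window.
- If it does not stand, restate 8.4 to the window actually observed, so that the DSMC knows how far the reports reach.

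The cost is a protocol amendment and, under the first route, one contact or chart check per subject, 20 in all. A few more background SAEs from the post-operative course will be listed.
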